**Methods:**

A randomized controlled trial will be conducted to assess the effectiveness of the intervention among pregnant women or their partners in Uganda’s central region, including the capital of Kampala. Seven hundred pregnant women (12–35 gestational weeks) or their partners will be recruited. All participants will receive access to a committed mobile money health savings account provided by a local organization that also offers savings targets and reminders for antenatal care appointments and health tips as part of a “Mamas Program” offered to expectant mothers. The time period in the intervention is from the day of enrollment until two weeks after the delivery date. The control group will receive the standard Mama Program offering. The intervention group will receive the standard Mama Program offering plus behavioral designs encouraging savings behavior through short-message service (SMS) text messages. The primary outcome is usage of maternal health services measured by level of birth preparedness and delivery at a health facility. Secondary outcomes include male involvement in maternal healthcare, measured by financial support, as well as total savings for healthcare, assessed using the validated amount of savings accrued in participants’ clinicPesa accounts from the day of enrollment plus any withdrawals for healthcare expenditures during the intervention period.

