### Study design

We will conduct a randomized controlled trial (RCT) to test the effectiveness of the intervention comprised of a behaviorally informed mobile money health savings account on birth preparedness, maternal health service utilization, male involvement in maternal health, and savings amount towards healthcare costs. A dedicated mobile money health savings account will be provided by clinicPesa, a mobile money health savings company registered in Uganda. clinicPesa offers a commitment device for savings, where a client’s savings can only be spent on healthcare expenditures and not withdrawn for other purposes. The overall study flow chart is shown in Fig. 1. The schedule of the RCT is shown in the Standard Protocol Items: Recommendations for Intervention Trials (SPIRIT) figure (Fig. 2). The SPIRIT checklist is provided in Additional file 1.

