### Outcomes

The primary outcome is level of birth preparedness and usage of maternal health services, assessed by the number of birth kits or items within birth kits purchased, antenatal care visits, skilled birth attendance by a doctor, nurse, midwife, and/or medical assistant or clinical officer, and delivery at a health facility, all based on recall by the participant; the amount of validated expenditure in participants’ clinicPesa accounts from the day of enrollment during the intervention period will also be assessed. The primary outcome will be measured by asking the participant during the end-line survey about their pregnancy and delivery experience.

Secondary outcomes include male involvement in maternal healthcare, measured by financial support, attendance to ANC, assisting with planning the delivery, and providing perceived emotional support to the mother, as well as total savings for healthcare, assessed using the validated amount of savings accrued in participants’ clinicPesa accounts from the day of enrollment plus any withdrawals for healthcare expenditures during the intervention period. The withdrawals will also be coded to determine if they were used for maternal health service costs, including transport, or other healthcare costs, such as birth preparedness kits, baby materials, or others. Deposits into the account will be coded by whether it was the mobile money account owner or another mobile money account (for example, a different family member saving into the account).

Male involvement in maternal healthcare will be assessed by measuring whether they provided financial support for clinicPesa or otherwise, attendance to ANC, and assisting with planning of the delivery, measured by an ad-hoc male involvement index [45]. Women will be queried about the perceived levels of involvement, and men will be queried about their level of involvement.

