## Discussion

The research study may demonstrate that behavioral insights can be used to financially empower mothers or their partners in Uganda to save towards pregnancy, thereby improving birth preparedness and other health outcomes. This approach could be an ideal option when encouraging future parents to save for their family as it is embedded into an existing infrastructure of the country.

There are several limitations in the present study. First, the local partner organization at time of publication is only registered to operate with private health facilities in the central region of Uganda, which is highly populous and excludes those who live in rural areas outside of Kampala. Considering the prevalence of maternal mortality in other regions of Uganda and persons attending public health facilities for health care, the study likely does not include hard-to-reach populations. Second, the mobile money health savings account validated amounts does not include savings that could be saved elsewhere, such as in cash or a traditional bank account. While the end-line questionnaire attempts to account for this, amounts could be inaccurate due to recall bias and social desirability with savings amounts outside of the mobile money savings account stated as higher than they are. Third, some participants may be lost to follow up because the end-line questionnaire is phone-based. However, a phone-based end-line survey was determined to be suitable for post-delivery, and the COVID-19 pandemic may also restrict in-person meetings. Lastly, findings of the study are focused on one locality and could be transferrable to other countries or organizations only if they also operate a committed mobile money health savings account.

The results would provide the Government of Uganda and other development organizations with evidence for strengthening programs focused on increasing access to maternal health services, improving birth preparedness, and investing in health financing. The initiative can also inform other countries that are seeking to encourage individual and family savings towards maternal health; increased birth preparedness and service utilization for maternal health care and involvement of male partners in maternal health were two areas of interest covered by this study. The research will contribute to the growing body of research connecting the importance of behavioral insights, empowerment, and human rights through health in a sustainable manner.

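### Spending from the clinicPesa account is listed in the sentence defining the primary outcome, but the intervention pushes money into that account, so this measure can rise without more use of maternal care

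*Protocol article*

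**What the plan says.** All references are to the protocol article.

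- **Outcomes, the construct.** "The primary outcome is level of birth preparedness and usage of maternal health services". The components listed are birth kits or kit items, antenatal visits, skilled attendance and facility delivery, all by participant recall. After a semicolon, the same sentence adds that validated expenditure in participants' "clinicPesa accounts from the day of enrollment during the intervention period will also be assessed".
- **Outcomes, the next sentence.** "The primary outcome will be measured by asking the participant during the end-line survey about their pregnancy and delivery experience". Account records are not a survey item; the Data collection section says they are pulled from the company's database.
- **Abstract, Methods.** "The primary outcome is usage of maternal health services measured by level of birth preparedness and delivery at a health facility". Account expenditure is not mentioned.
- **Data analysis.** Use of money for pregnancy-related health costs is listed as an outcome separate from birth preparedness and from service utilization.
- **What is randomized.** Both arms hold the same account and receive the standard programme. The intervention arm gets this "plus behavioral designs encouraging savings behavior through short-message service (SMS) text messages" (Abstract, Methods; also Intervention).
- **What the account allows.** A client's "savings can only be spent on healthcare expenditures and not withdrawn for other purposes" (Study design). The limit is healthcare, not maternal care.
- **Coding of withdrawals.** Under the secondary outcomes, withdrawals are coded as maternal service costs, including transport, or as "other healthcare costs, such as birth preparedness kits, baby materials, or others".
- **Stated limitation.** The Discussion says that "the mobile money health savings account validated amounts does not include savings that could be saved elsewhere". It makes this point for savings, not for spending.

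**The concern.** The primary outcome is meant to show whether families prepared for birth and used services. Expenditure through one payment channel is a proxy for that, and the randomized intervention acts directly on the channel. A family nudged to save in the account, which then pays from it for a delivery it would otherwise have paid for in cash, shows higher account expenditure for identical care. Spending on healthcare unrelated to the pregnancy has the same effect unless it is coded out.

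If expenditure is read as a component of the primary outcome, a difference between arms on that component could be reported as more use of maternal care when only the way of paying changed. Blinding of participants, assessors and the analyst does not protect against this, because the problem lies in what is measured. The measure is also likely to be prominent: it is the only item in the primary-outcome sentence not based on recall, and the Data analysis section expects account savings data to be available even when the end-line survey is not completed.

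**Working it through.** **1. Is expenditure part of the primary outcome?** The places set side by side:

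| Place | Points to |
|---|---|
| Outcomes, defining sentence | Included, as something also assessed |
| Outcomes, next sentence | Not included: measurement is by end-line survey |
| Abstract, Methods | Not included |
| Data analysis | Use of money is a separate outcome |

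The secondary outcomes begin only in the following paragraph, so the position of the expenditure clause suggests primary status while the other three places suggest a supporting role. The text does not settle it.

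**2. Does account expenditure measure service use?** Let T be a participant's total spending on maternity care, s the share paid through the account, and O other healthcare spending through the account. Then

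account expenditure = s × T + O.

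The nudges act on money entering the account, so they can raise s or O with T and the care received unchanged. Coding withdrawals by purpose can remove the non-maternal part of O. It cannot detect a change in s, because a displaced cash payment for a delivery is coded as a delivery cost either way.

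**3. How large could the effect be?** The document gives no value for s in either arm, so these figures are illustrations on assumed shares. With T equal in both arms and O = 0, the ratio of account expenditure is s(intervention) / s(control):

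- 20% versus 22%: 0.22 / 0.20 = 1.10, a 10% rise with no change in care.
- 20% versus 30%: 0.30 / 0.20 = 1.50, a 50% rise with no change in care.

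**4. Could a difference of that kind be statistically significant?** Inputs: 286 per arm (Sample size section); two-sided 5% (the level is stated, two-sided is assumed); T = UGX 100,000 per participant (assumed; scaled to the upper figure the Background gives for a mother's contribution at a facility delivery); standard deviation of account expenditure assumed at three values. The chance of significance is approximately Φ(d / SE − 1.96), with SE = SD × √(2/286) = SD × 0.0836.

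For 20% versus 30%, d = 0.10 × 100,000 = UGX 10,000:

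- SD 25,000: SE = 2,091; 10,000 / 2,091 = 4.78; chance 99.8%.
- SD 50,000: SE = 4,181; 10,000 / 4,181 = 2.39; chance 67%.
- SD 100,000: SE = 8,362; 10,000 / 8,362 = 1.20; chance 22%.

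For 20% versus 40%, d = UGX 20,000, and the chances are above 99%, 99.8% and 67%. With no shift in share the chance is 5%. In every case the true difference in care is zero.

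**5. The plan's own figure.** The only computed design figure is the minimum of 572 participants. It cannot be reproduced, because the rates assumed are not given, and nothing in this point depends on how it was derived.

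**The case against.** The strongest reply is that expenditure is not primary at all. The recalled components end at the semicolon, expenditure is something also assessed, the next sentence confines measurement to the survey, the abstract omits it, and the analysis lists use of money separately. Much of this stands. A reader might infer that a primary endpoint is biased by construction; the document does not support that, because it leaves the status of the measure unclear and nothing in it lets expenditure alone decide success. What remains is that the defining sentence still carries the measure and has to be reconciled with the other places.

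Further objections, and what stands of each:

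- **Extra account spending may be real extra care.** True, and that is the trial's hypothesis. But the measure cannot tell new care from displaced cash. The recalled items have no such mechanical link, so expenditure moving without them would be a warning sign.
- **Non-maternal spending is already dealt with.** Largely so: withdrawals are coded, and the Data analysis section names pregnancy-related costs. That restriction is not attached to expenditure where it appears in the primary-outcome sentence.
- **Birth kits.** A reader might infer a contradiction, since Outcomes puts kits under other healthcare costs while Data analysis counts preparation as pregnancy-related. The first separates services from goods; the second is a broader heading. A kit can be both a non-service cost and pregnancy-related.
- **Withdrawals inside total savings.** A reader might infer improper double counting. Adding withdrawals back is correct; otherwise those who saved and then spent would look like non-savers. Related primary and secondary outcomes are not an error.

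**Conclusion.** The point holds as one of construct validity joined to an unclear outcome hierarchy. Account expenditure sits in the sentence that defines the primary outcome, other parts of the article imply that it is not primary, and as a measure of service use it is open to bias towards the intervention through a change of payment channel or through non-maternal spending.

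The direction follows from the design, provided the nudges do raise payment through the account. The size is unknown. The 10% and 50% rises and the 22% to 99.8% chances of significance for a 20% versus 30% shift rest wholly on assumed shares, spending and standard deviations; they show that the effect could matter, not that it will. The recalled preparedness and service-use items are not affected by this mechanism.

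**What to change.** 1. In Outcomes, state that the primary outcome consists only of the preparedness and service-use items: birth kits or kit items, antenatal visits, skilled attendance and facility delivery. This brings the defining sentence into line with the survey-measurement sentence that follows it.
2. Move clinicPesa expenditure to the secondary outcomes, or label it a process measure of platform use. Analyse it as the pregnancy-related withdrawals already named in Data analysis, and say explicitly that kits and preparation are included, so that restricting to the maternal-service code does not drop them.
3. State that a difference in account expenditure alone will not be interpreted as increased use of maternal care.
4. Report savings held elsewhere, which the end-line questionnaire already tries to capture, as a sensitivity analysis carrying the Discussion's caveat on recall and social desirability. Main conclusions should not be moved onto recalled all-source spending: that caveat would apply with equal force, and the article does not say that the end-line collects such spending.

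**Cost.** Items 1 to 3 are wording only, and item 4 uses information the end-line already seeks. An effect on sample size cannot be computed because the basis of 572 is not given; the section refers to earlier research on service utilization, not to account spending. The real downside is that the primary outcome then rests on recalled items only, collected in a phone survey, with no database-validated component.

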### Sample size, eligibility, and recruitment

The minimum sample size for the RCT is 572 participants (286 in each arm). It was calculated using OpenEpi version 3. The power of the study was set at 80% and the significance level at 5%. A previous savings group research in a SSA region for maternal healthcare service utilization was used for assumptions [43]. Considering an approximate 20% dropout rate and sampling unit rounding, 700 participants will be recruited (350 participants in each arm).

To be eligible for joining in this study, participants should have the following characteristics: (1) 18–49 years old, (2) between 12–35 gestational weeks (pregnant female) OR partner of someone who is (male), (3) own a mobile phone, (4) has a registered Mobile Telephone Network (MTN) mobile money account, (5) willingness to enroll in clinicPesa’s health savings mobile money account. Participants are ineligible if their partner is known to already be participating in the study to avoid duplicating results of savings amounts; only one member per household may participate in the study.

Participants will be recruited and enrolled in person by clinicPesa at 77 public and private health facilities where clinicPesa operates. Five trained research assistants will approach male and female clients at the maternity ward of selected health facilities. The clients at the health facility will be offered an opportunity to enroll in the study when they sign up to join clinicPesa. In the case of a COVID-19 lockdown on movement, participants will be recruited through a phone query from clinicPesa’s registered user base. Users who sign up for clinicPesa agree to terms and conditions set by clinicPesa, which include the possibility of being offered to join studies to improve the product offered by clinicPesa.

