### Randomization

A person who is not involved with any other study procedure (including recruitment, implementation of the intervention, and data analysis) will share a computer-generated randomized allocation table with clinicPesa at the beginning of the recruitment period, which will not be shared with the study recruitment team [44]. At the end of each recruiting day, the customer ID numbers of participants who agreed to join the study will be matched to the table to be assigned to either the control or the intervention group (1:1 randomization), and a study participant ID will be created to maintain participant anonymity within the study [32].

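### The savings and expenditure windows open on the day of enrollment but the arm is assigned only at the end of that day, so earlier same-day transactions count as outcome: no bias, a precision cost of unknown and possibly negligible size, and a cheap remedy

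*Protocol article*

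**What the plan says.** All references are to the protocol article.

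- **Outcomes, savings (secondary).** Total savings is taken from "clinicPesa accounts from the day of enrollment plus any withdrawals for healthcare expenditures during the intervention period". The abstract's Methods paragraph defines it in the same way.
- **Outcomes, expenditure (listed with the primary outcome).** "the amount of validated expenditure in participants’ clinicPesa accounts from the day of enrollment during the intervention period will also be assessed".
- **Abstract, Methods.** "The time period in the intervention is from the day of enrollment until two weeks after the delivery date".
- **Sample size, eligibility, and recruitment.** On the in-person route, "The clients at the health facility will be offered an opportunity to enroll in the study when they sign up to join clinicPesa". Under a COVID-19 lockdown, people who are already registered users are recruited by phone instead.
- **Randomization.** "At the end of each recruiting day, the customer ID numbers of participants who agreed to join the study will be matched to the table", and the arm is assigned at that point.
- **Intervention.** Participants in both arms can deposit and withdraw.
- **Data analysis.** Mean total savings are compared between arms by t-test, and mixed-effect regression is planned for savings and the other outcomes.

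Nothing in the article removes transactions made on the enrollment day before allocation. Nothing says that an opening deposit is made or required.

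**The concern.** The window start is stated, so this is not a detail left open for an analysis plan. As stated, the window opens some hours before the arm exists. A client who opens an account in the morning, deposits, and perhaps pays for that day's visit from it has produced account data that no later message can influence. Those amounts still enter the savings and expenditure totals.

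What is at stake is precision. Amounts unrelated to the arm generally add variance to the comparison, and the unadjusted t-test does nothing to take it out. The savings comparison is also the most direct test of whether the messages change behavior, and the account measures are the ones the article describes as validated.

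**Working it through.** **1. Order of events.** The outcome window opens on the calendar day of enrollment. Consent and, on the in-person route, account sign-up occur during that day. Allocation follows at the end of the day. The gap is less than one day, and same-day transactions before allocation lie inside the outcome window in both arms.

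**2. Bias.** Write total = pre + post, where pre is the amount before allocation and post the amount after it. Randomization makes pre independent of arm, so the expected difference in totals equals the expected difference in post. A simulation with 4,000 replicates, 286 per arm, r = 0.3 and rho = 0 gave a mean difference of 0.233 SD with the pre-allocation part and 0.234 SD without it. There is no bias.

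**3. Inputs for precision.** The article gives no deposit amounts, no SD of savings and no correlation, and it has no power figure for savings to reproduce. Its 80% power and 572 participants (286 per arm) rest on a study of maternal service use. The following are therefore assumptions:
- r = SD(pre) / SD(post), and rho = their correlation.
- Reference: 286 per arm, two-sided 5%, and a difference that post alone would detect with 80% power. That difference is (1.960 + 0.842) × sqrt(2/286) = 0.234 SD.

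**4. Formulas.** Variance of the total relative to post alone: V = 1 + r² + 2·rho·r. Power = Phi(2.80/sqrt(V) − 1.96).

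| r | rho | V | Power |
|---|---|---|---|
| 0 (no same-day transactions) | – | 1 | 80.0% |
| 0.1 | 0 | 1.01 | 79.6% |
| 0.3 | 0 | 1.09 | 76.5% |
| 0.5 | 0 | 1.25 | 70.7% |
| 0.1 | 0.3 | 1.07 | 77.3% |
| 0.3 | 0.3 | 1.27 | 70.1% |
| 0.5 | 0.3 | 1.55 | 61.4% |
| 0.1 | −0.3 | 0.95 | 82.0% |
| 0.3 | −0.3 | 0.91 | 83.6% |

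V is below 1 exactly when r² + 2·rho·r < 0, that is, when rho < −r/2. In that region the stated window is more precise than one that starts at allocation without adjustment.

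**5. Effect of the covariate.** With post as the outcome and pre as a linear covariate, the residual variance is 1 − rho². The stated window without adjustment has

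V = 1 + r² + 2·rho·r = (r + rho)² + (1 − rho²).

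Since (r + rho)² cannot be negative, the adjusted analysis is never less precise, whatever r and rho are, apart from one degree of freedom. On the same reference it gives 83.6% power at rho = 0.3 or −0.3 and 89.9% at rho = 0.5.

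**The case against.** **The gap is tiny and may hold almost nothing.** Assume delivery at 40 weeks. Enrollment at 12 to 35 weeks with follow-up to two weeks after delivery then gives (40 − 12 + 2) × 7 = 210 days down to (40 − 35 + 2) × 7 = 49 days. If daily amounts were independent with equal variance, r would be about 1/sqrt(210) = 0.07 to 1/sqrt(49) = 0.14, and power 79.8% to 79.2%. An opening lump sum could make r larger, but the article does not mention one. This stands: the loss may be negligible.

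**The 80% reference is not the trial's own for savings.** This stands too. Savings data can be extracted without the end-line survey, so up to 350 per arm may contribute. For the same 0.234 SD difference that gives about 87% power, and about 79% even at r = 0.3, rho = 0.3.

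**The correlation could be negative.** Both arms can set savings targets, so an early deposit might reduce later saving. This cannot be excluded. It means that moving the window alone is not guaranteed to help, which is why the covariate belongs with it.

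**Stronger readings that the document does not support.** A reader might infer that the comparison is biased; step 2 of the working shows that it is not. A reader might infer a loss of 10 to 19 power points; that needs r = 0.3 to 0.5 with rho = 0.3, and the article supports neither value. A reader might infer that the effect is diluted. Only a ratio of means would shrink; the planned t-test compares a difference in means, whose expectation is unchanged. A reader might infer that every participant is affected. Only those who transact that day before allocation are, and users recruited by phone have already signed up, so they have no opening deposit that day. The recalled components of the primary outcome do not use this window.

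**Covariates can be left to the analysis plan.** That is fair: their absence from the article is no fault. With pre as a linear covariate, regressing the total or post on arm gives the same treatment estimate, so the gain in step 5 comes from the covariate. What remains for the article is the stated window start, which matters for the unadjusted t-test and for what the outcome means.

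**Conclusion.** The point holds in a small form. The order of events is plain from the text: the savings and expenditure windows open before the arm is assigned, and nothing excludes what happens in between. The consequence is confined to precision on the account-based measures. Its size cannot be determined from the document. It ranges from nil, through a fraction of a power point when same-day amounts vary little (r = 0.1, rho = 0), to about ten points in a case that the article gives no reason to expect (r = 0.3, rho = 0.3), and it turns into a gain when rho is below −r/2. All these figures rest on an assumed 80% reference and assumed values of r and rho. This is a minor, optional improvement, worth making because it costs almost nothing and does not require knowing either value.

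**What to change.** In the abstract and the Outcomes section, define total savings, and in the Outcomes section validated expenditure, as counted from the recorded allocation time, or from the day after enrollment if the account records hold only dates. In the regressions on savings and expenditure, include the pre-allocation amount as a baseline covariate. Make both changes together and rely on the adjusted regression for precision, since an unadjusted t-test on the later window could lose slightly if rho is below −r/2. Fix the wording before the savings data are analyzed, so that the window is not chosen after results are seen.

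The cost is about one sentence of wording, a time or date filter on records that are already to be drawn from the account database, one covariate and one degree of freedom. No added participants or data collection are needed. If only dates are stored, a few deposits between allocation and midnight are dropped from the outcome, and the enrollment-day total used as covariate is only approximately a pre-allocation value.

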### Other information

The following information will be collected during the baseline interviews to conduct sub-group analyses and to identify factors associated with savings for maternal healthcare and male involvement during pregnancy: age, education, employment, area of residence (rural or urban), pregnancy intention, joint decision making within a couple. Other information, such as feedback on the intervention, will be collected to inform future interventions, but this information will not be part of the analysis for this study.

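### One male-involvement index combines women's perceptions with men's self-ratings, and enrolled men report care by proxy, but the analysis names no term for respondent role

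*Protocol article*

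**What the plan says.** All of this is in the protocol article.

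- **Who reports.** Under Sample size, eligibility, and recruitment, a participant is either a woman at 12 to 35 weeks of pregnancy or the male partner of such a woman, and "only one member per household may participate in the study". No household has paired reports. The share of men is neither stated nor capped.
- **Male involvement (secondary).** Outcomes describes it as "measured by an ad-hoc male involvement index", and then says: "Women will be queried about the perceived levels of involvement, and men will be queried about their level of involvement". The index content is given as "measuring whether they provided financial support for clinicPesa or otherwise, attendance to ANC, and assisting with planning of the delivery". An earlier sentence of the same section lists these three components plus perceived emotional support.
- **Primary outcome.** The items are birth kits, antenatal visits, skilled attendance and "delivery at a health facility, all based on recall by the participant". They are collected by "asking the participant during the end-line survey about their pregnancy and delivery experience", with no separate provision for male participants.
- **Analysis.** Data analysis compares the arms on the primary outcome and uses mixed-effect regression for savings, birth preparedness, service use and male involvement. It names no respondent-role term.
- **Baseline factors.** Other information names "age, education, employment, area of residence (rural or urban), pregnancy intention, joint decision making within a couple" for sub-group analyses and for factors associated with savings and male involvement. Data collection gives a second list, for savings behaviour, which includes pregnancy status.

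**The concern.** For an enrolled man, the index is a rating of his own conduct, and he is the person who receives the messages. For an enrolled woman, it is her view of someone who was not enrolled and whose phone was not messaged. These are two measurements under one name. The first carries a direct effect of the messages and the second a spill-over effect. A pooled arm difference averages them in a proportion set by whatever share of men happens to enrol.

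There is also a route to bias that randomisation does not close. Messages that encourage saving for the birth may lead men in the intervention arm to rate themselves higher without any change in conduct. The protocol's Discussion raises social desirability only for savings held outside the account.

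The primary outcome is touched in a different way. An enrolled man's account of his partner's antenatal visits, birth attendant and place of delivery is a proxy report. Savings and expenditure drawn from the provider's database are not affected.

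**Working it through.** **The plan's own figure.** The minimum of 572 (286 per arm; 80% power, 5%) cannot be rebuilt because the article gives no event rates. One of many compatible pairs is 50% against 61.6%, which gives 287 per arm. The figure is not disputed; 286 per arm is used only as the scale below.

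**Assumed inputs, not in the documents.** Share of men *m*; gap *D* between the mean index of men and women, in within-role SDs; equal within-role variance; two-sided test.

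**1. What the pooled effect means.** Pooled effect = m × (effect on men's self-rating) + (1 − m) × (effect on women's perception). If men in the intervention arm overrate themselves by an assumed 0.25 SD and nothing else changes, the pooled effect is 0.25 × m: 0.025 SD at m = 0.1, 0.10 SD at m = 0.4 and 0.125 SD at m = 0.5.

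**2. Precision of the index without a role term.** The variance factor is 1 + m(1 − m)D². The effect detectable at 286 per arm is 2.802 × √(2/286) = 0.234 SD. Unadjusted power is Φ(2.802/√factor − 1.96).

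| m | D | Variance factor | Efficiency | Power |
|---|---|---|---|---|
| 0.4 | 0.5 | 1 + 0.24 × 0.25 = 1.06 | 1/1.06 = 0.94 | Φ(0.762) = 0.78 |
| 0.4 | 1.0 | 1 + 0.24 × 1 = 1.24 | 1/1.24 = 0.81 | Φ(0.556) = 0.71 |

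Over m = 0.1 to 0.5 and D = 0.3 to 0.8, power runs from 0.797 down to 0.739, a loss of about 0 to 6 points.

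**3. Chance imbalance in the share of men.** The SD of the arm difference in male share at m = 0.4 is √(2 × 0.24/286) = 0.041. The 95% limit is 1.96 × 0.041 = 0.080, which moves the index by 0.08 SD at D = 1 and 0.04 SD at D = 0.5. This is not a further loss. The variance of the arm difference is (2/286) × [1 + m(1 − m)D²], and its second part, 2m(1 − m)D²/286, is exactly the variance of D times the imbalance. Steps 2 and 3 describe one quantity.

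**4. Proxy error on a binary primary item.** If men report with sensitivity *se* and specificity *sp*, equal in both arms, the arm difference shrinks by the factor (1 − m) + m(se + sp − 1). With assumed true rates of 0.50 and 0.6165 (difference 0.1165):

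- m = 0.1, se = sp = 0.95: factor 0.99, power 0.795.
- m = 0.3, se = sp = 0.90: factor 0.94, power 0.751.
- m = 0.5, se = sp = 0.80: factor 0.80, difference 0.093, power 0.610.

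**5. What a split by role can show.** For an effect of 0.234 SD, power among men alone is 0.14, 0.34 and 0.51 at m = 0.1, 0.3 and 0.5. The interaction at m = 0.4 has standard error √[(2/286)(1/0.4 + 1/0.6)] = 0.171, so 80% power needs a difference between roles of 2.802 × 0.171 = 0.48 SD.

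**The case against.** The strongest reply is that an article leaves covariates, sub-group models and randomisation details to the full protocol or analysis plan, and neither is shown. That is fair for the covariate taken alone. The article also does not say that the allocation table is unstratified. What it does fix is the outcome definition: one index fed by two kinds of report, and primary items resting on the enrolled person's recall. A covariate added elsewhere would not make the two reports one measure.

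Pregnancy status, in the Data collection list, could serve as respondent role, since every eligible woman is pregnant and every other participant is a male partner. This stands in part, but that list is tied to savings behaviour, not to male involvement or the primary outcome.

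A reader might infer several stronger points that the text does not support:

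- *Chance imbalance in the share of men biases the effect.* Under randomisation it is random error, already in the standard error.
- *Role was left out of the covariate lists.* The lists in Other information and Data collection name sub-group and associated factors; they are not model specifications.
- *The arms are compared on one pooled mean of the index.* Means and t-tests are assigned to total savings; male involvement goes to regression.
- *A woman's partner must deposit from another account to count as giving financial support.* The item covers "measuring whether they provided financial support for clinicPesa or otherwise, attendance to ANC, and assisting with planning of the delivery", so support outside the account also counts, and its scoring is not described.
- *The Abstract contradicts Outcomes by naming only financial support.* That is condensation.

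**Conclusion.** The point holds as a moderate one that should be acted on. The plan as written pools two different reports of male involvement and takes some primary items from proxies, with no named term for role. Pooling does not by itself bias the arm comparison.

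The main harm is to interpretation. A pooled rise in male involvement could reflect men's own conduct, women's perception of partners who were not enrolled, or inflated self-report by messaged men, and the pooled figure cannot tell these apart. The loss of precision is smaller: 6% extra variance at a 0.5 SD role gap and 24% at 1 SD, both with an assumed 40% men, on a secondary outcome that the article does not tie to the sample size. Proxy error could cost a binary primary item from almost nothing to about 19 power points, but the upper end needs half the sample to be men and reporting accuracy of only 80%. All these sizes rest on the share of men, the role gap and the proxy accuracy, none of which the article gives.

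**What to change.** - **Covariate.** Include respondent role (pregnant woman or partner) as a fixed covariate in the primary and secondary models. Role is known at enrolment from the eligibility criteria, so this needs no new data and costs one parameter per model. It recovers the precision lost to a role gap. It does not correct proxy misreporting, which should be stated as a limitation of the recalled primary items.
- **Male involvement.** Keep all randomised participants in the intention-to-treat analysis. Also report the arm effect separately for women's reports and men's self-reports, with an arm-by-role interaction, and say in advance that the interaction has low power and that a null result does not show the two effects are equal.
- **Index content.** Reconcile the two item lists in Outcomes: perceived emotional support is in the sentence defining the secondary outcome and absent from the sentence defining the index.

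Making women's reports the main analysis of male involvement is an option, not a requirement. It would set aside randomised men and reduce precision, in tension with the intention-to-treat commitment.
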